## Abstract

**Background::**

Post-stroke depression (PSD) is one of the most common stroke complications with high morbidity. Researchers have done much clinical research on Traditional Chinese Medicine (TCM) treatment, but very little research on diagnosis. Based on the thought of combination of disease and syndrome, this study will establish a unified and objective quantitative diagnosis model of TCM syndromes of PSD, so as to improve the clinical diagnosis and treatment of PSD.

**Objective::**

First: To establish a unified and objective quantitative diagnosis model of TCM syndromes in PSD under different disease courses, and identify the corresponding main, secondary, and concurrent symptoms, which are based on the weighting factor of each TCM symptom. Second: To find out the relationship between different stages of PSD and TCM syndromes. Clarify the main syndrome types of PSD under different stages of disease. Reveal the evolution and progression mechanism of TCM syndromes of PSD.

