In summary, this study is aiming to establish a unified and objective quantitative diagnostic standard of TCM for specific syndromes in different stages of PSD, and to clarify the evolution and progression law of PSD syndromes. These achievements will play great roles in promoting the standardized research of PSD TCM syndrome diagnosis and improving clinical diagnosis and treatment.

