### Research type

2.3

This is a retrospective study of PSD TCM diagnosis.

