### Recruitment

2.4

This study will recruit a total of 300 PSD patients who were hospitalized patients in the First Teaching Hospital of Tianjin University of TCM with complete cases from January 2014 to January 2019. The recruitment started on 1st November 2020, and is expected to be completed on 31st October 2021.

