### Sample size estimation

2.11

Since Back Propagation (BP) artificial neural network is the core method for the construction of syndrome model in this study, this method needs a large amount of data support in the parameter fitting process, and there is no exact method to calculate the sample size at present. According to some relevant studies,^[11–14]^ it is suggested that sample size should be not less than 200. Combined with the admission status of PSD in this hospital and 20% verification data, this study plans to collect 300 cases.

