### Statistical methods

2.12

Demographic data, general physical examination, laboratory examination, imageological examination, 4 diagnostic methods information of TCM Inspection, and original prescription of TCM are input by SPSS17.0 software. All data information is converted into numbers, and there is no text information except the variable names. The coding principle of grade data is the occurrence probability of each variable grade. The assignment principle of qualitative variables is 1 for existence and 0 for nonexistence.

The TCM diagnostic information in the clinical data is included in the analysis. Factor analysis is used to extract the syndrome elements and targets of PSD in different stages (acute stage, consolidation stage, maintenance stage, and withdrawal stage). Principal component analysis is performed for each group. According to the values of gravel map and characteristic root, the significant common factors are extracted. According to the symptom indexes of common factors, the syndrome elements are classified and their targets are defined. According to the PSD associated indexes of traditional Chinese and western medicine combining with disease and syndrome, the main PSD syndrome types and the main TCM symptoms under specific syndromes are determined. Based on BP artificial neural network, the quantitative diagnosis model of TCM syndromes in PSD will be established (Fig. 1).

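### The objective of revealing how syndromes evolve and progress goes beyond the stated analysis, which supports only a between-group association of PSD stage and TCM syndrome among inpatients

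*Protocol article*

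**What the plan says.** The abstract's Objective section names two aims. The first is the quantitative diagnosis model. The second covers the relation between stage and syndrome and the main syndrome types at each stage, and ends with "Reveal the evolution and progression mechanism of TCM syndromes of PSD". The last paragraph of the Introduction restates the ambition: "to clarify the evolution and progression law of PSD syndromes".

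The methods are these:

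- Section 2.3: "This is a retrospective study of PSD TCM diagnosis".
- Section 2.4: "This study will recruit a total of 300 PSD patients who were hospitalized patients", at one hospital, "with complete cases from January 2014 to January 2019".
- Section 2.8 lists the stage of PSD as one indicator, without time points. It also lists the TCM syndrome of stroke and of PSD.
- Section 2.11: "this study plans to collect 300 cases".
- Section 2.12 extracts syndrome elements by factor analysis "in different stages (acute stage, consolidation stage, maintenance stage, and withdrawal stage"), applies principal component analysis to each group, and then fits the neural network.

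The limitations in section 3.1 name incomplete records and the single region, and nothing about reading stage differences as change over time.

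**The concern.** Evolution and progression are statements about what happens to a patient over time, and a mechanism is a statement about why. Separate analyses of stage groups describe which symptoms cluster at each stage. They do not say whether patients move from one syndrome to another, in which direction or how often.

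The patients are also all inpatients of one hospital. If the chance of being in hospital at a given stage depends on the syndrome, the syndrome mix will differ between stages even where no patient's syndrome has changed.

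At stake is the conclusion drawn. Section 4 expects the results to be of use to clinicians and guideline developers. If stage differences were published as a law of progression, readers would take a comparison of groups for a description of the disease course.

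**Working it through.** The point concerns design, so the main check sets the objective beside the analysis.

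**1. The plan's own figure.** The article plans 300 cases, and on the minimum it says "it is suggested that sample size should be not less than 200". With 20% kept for verification, 300 × 0.80 = 240 remain, which is at least 200. Inflating 200 for the 20% gives 200/0.80 = 250 or 200 × 1.20 = 240, not 300. However, the 300 also rests on the hospital's admissions, which are not quantified, so there is no closed formula to reproduce. None of this bears on the point.

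**2. Observations per patient.** Section 2.4 gives 300 patients and section 2.11 gives 300 cases: 300/300 = 1.0 case per patient. A case here appears to mean a patient's record, and a record may hold more than one assessment. The ratio therefore does not settle how many observations each patient contributes.

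**3. What the stated analysis yields under each reading.**

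| Reading of the data | What the per-stage analysis gives |
|---|---|
| Each patient is in one stage | Comparison of different patients; no within-patient information |
| Some records span several stages | Possible within-patient information, but separate analyses per stage do not use the pairing |
| Each patient has a syndrome at stroke and one at PSD | A possible pair from stroke to depression, not across the four PSD stages; section 2.12 describes no paired use |

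The analysis described does not link stages within a patient under any of the three.

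**4. Why stage-wise results do not identify transitions.** Let p1 and p2 be the share with a given syndrome at two stages. Even if the same patients were seen at both,

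p2 − p1 = (share moving into the syndrome) − (share moving out of it).

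Only the difference is determined. Equal shares are compatible with no movement or with equal movement both ways.

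**5. Why admission matters.** Suppose a syndrome has true share p at every stage, and patients with it are r times as likely as others to be inpatients at one stage. The share observed there is

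p × r / (p × r + 1 − p),

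which equals p only if r = 1 (for p strictly between 0 and 1). With any other r an apparent shift appears without any patient changing. The article gives neither p nor r, so the formula shows the direction of the problem and not its size in this study.

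**6. What the analysis does support.** The relation between stage and syndrome and the main types per stage, which are the other parts of the second objective, fit a per-stage analysis, read as statements about inpatients. The abstract's Methods section words the stage aim in these terms.

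**The case against.** The strongest reply is that the article does not say each patient contributes a single observation. Inpatient charts can contain serial notes, patients may have been readmitted within the five-year window, and section 2.8 lists a syndrome for stroke as well as for PSD. A reader might infer that the study rests on single snapshots and that no transition could ever be estimated from these data. The documents do not support that: the snapshot is an inference from 300 patients and 300 cases, and the same records might hold usable sequences. This part of the objection stands and limits the point to the analysis as stated.

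It can also be said that a journal article condenses a fuller protocol, so the absence of a transition model is not in itself a fault. That is right. The point does not rest on a missing detail. It rests on a stated objective that the stated analysis does not answer. The mention of long-term follow-up in section 2.6 does not close the gap: it occurs only in an exclusion criterion, no follow-up data are listed in sections 2.8 and 2.9, and the study is called retrospective.

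Finally, the disputed words are the last part of the second objective. The main product is the diagnostic model, and the article's own conclusions claim no law of progression. This stands too. A reader might infer that the study as a whole cannot meet its purpose, which the documents do not support.

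**Conclusion.** The point holds for the analysis as described. It supports a between-group association of PSD stage and TCM syndrome among inpatients of one hospital. It does not support within-patient evolution, and still less a mechanism or a law. Differences between stages may combine true change with differences in who is admitted.

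In extent, one part of one of two objectives is affected, along with its repetition in the Introduction. The diagnostic model, the sample size and the remaining stage objectives are untouched. No numerical bias can be given, since the article reports no stage split, syndrome prevalence or admission pattern. This should be fixed, but it does not stand in the way of the study.

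The conclusion assumes that section 2.12 describes the analysis fully as far as stage is concerned. If the full protocol specifies serial assessments and a within-patient analysis, the objective could stand in part, and the article should then say so.

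**What to change.** 1. In the abstract's Objective section and the last paragraph of the Introduction, restate this aim as the association between PSD stage and TCM syndrome among hospitalised PSD patients, and remove the references to evolution, progression, mechanism and law.
2. In section 3.1, add that differences between stages cannot be read as progression within patients, because they may also reflect which patients are in hospital at each stage.
3. Optionally, where the same records hold serial assessments or repeat admissions, link them and report within-patient syndrome transitions as a separate descriptive analysis, stating how many patients contribute.

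Adjusting the stage comparison for time since stroke would not be a substitute. It is not among the listed variables, it may track stage closely, and separate factor analyses contain no regression of syndrome on stage in which to adjust.

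Steps 1 and 2 cost only rewording, and the price is a more modest claim. Step 3 needs record linkage and further extraction from charts already in use. No new patients are needed.

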**Methods and analysis::**

This is a retrospective study of PSD TCM diagnosis. Three hundred patients who were hospitalized in the First Teaching Hospital of Tianjin University of TCM with complete cases from January 2014 to January 2019 are planned to be recruited. The study will mainly collect the diagnostic information from the cases, find the related indicators of TCM and Western medicine in PSD, and clarify the relationship between different disease stages and TCM syndromes. Finally, the PSD TCM syndrome quantitative diagnosis model will be established based on the operation principle of Back Propagation (BP) artificial neural network.

**Conclusion::**

To collect sufficient medical records and establish models to speed up the process of TCM diagnosis.

In summary, this study is aiming to establish a unified and objective quantitative diagnostic standard of TCM for specific syndromes in different stages of PSD, and to clarify the evolution and progression law of PSD syndromes. These achievements will play great roles in promoting the standardized research of PSD TCM syndrome diagnosis and improving clinical diagnosis and treatment.

## Methods and analysis

2

### Study registration

2.1

This study protocol was registered at www.chictr.org.cn (http://www.chictr.org.cn/showprojen.aspx?proj=62356) on October 19, 2020, before trial commencement (Trial registration number: ChiCTR2000039143). The patients will be selected from the medical records and fully informed of the benefits and potential disadvantages. Seeking prior consent is necessary, and they will be provided written informed consent.

### Ethics and dissemination

2.2

This study must be conducted in accordance with the declaration of Helsinki and relevant Chinese clinical trial research standards and regulations. Before the experiment begins, the ethics committee of First Teaching Hospital of Tianjin University of TCM approved the study. The results of the trial will be reported through peer-reviewed journals and conference presentations.

### Research type

2.3

This is a retrospective study of PSD TCM diagnosis.

### Recruitment

2.4

This study will recruit a total of 300 PSD patients who were hospitalized patients in the First Teaching Hospital of Tianjin University of TCM with complete cases from January 2014 to January 2019. The recruitment started on 1st November 2020, and is expected to be completed on 31st October 2021.

### Inclusion criteria

2.5

The diagnosis is consistent with PSD;The age is 18 to 75 years old, both male and female;The information of related cases is complete;The course of stroke is more than 14 days.

### Exclusion criteria

2.6

Patients with disturbance of consciousness and obvious mental retardation and aphasia;Patients with positive personal and family history of mental disorders;Patients with serious heart disease, heart failure, liver dysfunction, renal insufficiency, respiratory failure, malignant tumor, gastrointestinal bleeding, etc at the onset of the disease, they are not expected to complete the long-term follow-up;Pregnant and lactating women.

### Blind method

2.7

Data collection and recording will be done by Clinical Research Coordinator (CRC). The data statistics will be completed by a third party statistician.

### Main indicators

2.8

TCM syndrome of stroke and PSD;Four diagnostic methods information of TCM Inspection: tongue appearance, complexion, etc; Smelling: smelling halitosis and other abnormal body odor; Inquiring: sweating and defecation; Palpating: pulse condition, whether to touch gall, tumor, scrofula, and swelling;Original prescription of TCM;Score of TCM syndrome score scale;Stage of PSD.

### Secondary indicators

2.9

Demographic data: age, gender, height, weight, etc;Influencing factors of disease diagnosis: past history and combined medication;General physical examination;Laboratory examination;Imageological examination.

### Data collection

2.10

Researchers who collect patient information during the study will receive rigorous training. The date is collected and conducted in accordance with relevant regulations and standard operating procedures. The borrowed paper-based medical records and related materials will be stored and locked in dedicated area of hospital. The collected electronic information will be stored in dedicated computer or hard drive with password protection. The experimental information can be secured not to be exposed. The host of the project will be fully responsible for the confidentiality of the medical records.

### Sample size estimation

2.11

Since Back Propagation (BP) artificial neural network is the core method for the construction of syndrome model in this study, this method needs a large amount of data support in the parameter fitting process, and there is no exact method to calculate the sample size at present. According to some relevant studies,^[11–14]^ it is suggested that sample size should be not less than 200. Combined with the admission status of PSD in this hospital and 20% verification data, this study plans to collect 300 cases.

### Statistical methods

2.12

Demographic data, general physical examination, laboratory examination, imageological examination, 4 diagnostic methods information of TCM Inspection, and original prescription of TCM are input by SPSS17.0 software. All data information is converted into numbers, and there is no text information except the variable names. The coding principle of grade data is the occurrence probability of each variable grade. The assignment principle of qualitative variables is 1 for existence and 0 for nonexistence.

The TCM diagnostic information in the clinical data is included in the analysis. Factor analysis is used to extract the syndrome elements and targets of PSD in different stages (acute stage, consolidation stage, maintenance stage, and withdrawal stage). Principal component analysis is performed for each group. According to the values of gravel map and characteristic root, the significant common factors are extracted. According to the symptom indexes of common factors, the syndrome elements are classified and their targets are defined. According to the PSD associated indexes of traditional Chinese and western medicine combining with disease and syndrome, the main PSD syndrome types and the main TCM symptoms under specific syndromes are determined. Based on BP artificial neural network, the quantitative diagnosis model of TCM syndromes in PSD will be established (Fig. 1).

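### As written, section 2.12 codes graded variables by how common each grade is, which does not in general preserve severity order and can distort the factor analysis and symptom weights

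*Protocol article*

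**What the plan says.** Section 2.12 (Statistical methods) of the protocol article gives two coding rules, one after the other. For graded variables: "The coding principle of grade data is the occurrence probability of each variable grade". For qualitative variables: "The assignment principle of qualitative variables is 1 for existence and 0 for nonexistence". It also states that "All data information is converted into numbers, and there is no text information except the variable names", so the code is the value that enters the analysis.

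The same section then uses the TCM diagnostic information in two steps. First, "Factor analysis is used to extract the syndrome elements and targets of PSD in different stages", with "Principal component analysis is performed for each group" and factors kept according to the scree plot and eigenvalues. Second, "Based on BP artificial neural network, the quantitative diagnosis model of TCM syndromes in PSD will be established".

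The Objective in the abstract seeks main, secondary and concurrent symptoms, "which are based on the weighting factor of each TCM symptom". Those weights rest on the coded inputs.

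The article gives no formula or worked example for the grade code and does not list the graded variables. Nothing elsewhere in it modifies the rule.

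**The concern.** The frequency of a grade is not a measure of its severity. If each grade is replaced by its relative frequency, three things can go wrong.

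- **Merging.** Two grades that are equally common receive the same number and can no longer be told apart.
- **Direction.** The commonest grade receives the highest code. If absence is commonest, it scores highest, whereas absence scores 0 on the binary items in the same analysis.
- **Dependence on the sample.** If the probabilities are recomputed by stage, in the verification data or in new patients, the same grade takes a different number in each.

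Principal component analysis is linear in the codes, so it cannot recover an order that the code has scrambled. At stake are the syndrome elements extracted in each stage and the symptom weights, which are the study's main products. This is a rule that the article states, not a detail left to a fuller document.

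**Working it through.** The plan gives no figure to reproduce here. The coding and the later steps are taken from section 2.12. The grade frequencies are not in the article, so every distribution below is an assumption, written as the percentage in grades 0/1/2/3 (none to severe).

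**1. Correlation of code with severity.** Let grade g = 0, 1, 2, 3 have frequency p(g). The literal code is c(g) = p(g). Then

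r = [Σp·g·c − (Σp·g)(Σp·c)] / √[var(g)·var(c)].

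- *50/20/20/10.* Σp·g = 0.90, Σp·c = 0.34, Σp·g·c = 0.15. Covariance = 0.15 − 0.306 = −0.156. var(g) = 1.09, var(c) = 0.0264. r = −0.156/√0.02878 = **−0.92**. Grades 1 and 2 share the code 0.2.
- *10/40/35/15.* Covariance = 0.4725 − 1.55 × 0.315 = −0.01575. var(g) = 0.7475, var(c) = 0.012025. r = **−0.17**. None (0.10) and severe (0.15) lie side by side.
- *25/25/25/25.* The code is constant, so r is undefined and the variable carries no information.
- *10/20/30/40.* c is linear in g, so r = **+1.00**.

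A steadily falling pattern, 50/30/15/5, gives r = −0.99. This is almost a pure reversal with the order intact.

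**2. How often order survives.** If all frequency distributions are taken as equally likely (an assumption), every ordering of the k frequencies has probability 1/k!. The code rises with severity in 1/6 = 17% of three-grade and 1/24 = 4% of four-grade variables. It is monotone in either direction in 2/6 = 33% and 2/24 = 8%.

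**3. Conflict with the 0/1 items.** One graded and one binary symptom were simulated from a common factor (loading 0.7, binary symptom present in 40%). With ordered scores they correlate at +0.35 to +0.37. With frequency codes the correlation is −0.36 for 50/30/15/5, −0.03 for 20/30/30/20 and +0.35 for 10/20/30/40.

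**4. Effect on principal components.** Eight four-grade symptoms were simulated from one true factor (loading 0.7) in 100,000 simulated patients, so sampling error is negligible.

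| Setting | Code | First two eigenvalues | Eigenvalues above 1 | Loadings on first component | Correlation of first component with true factor |
|---|---|---|---|---|---|
| Mixed frequency patterns | Ordered 0-3 | 3.91, 0.64 | 1 | 0.69 to 0.71 | 0.92 |
| Mixed frequency patterns | Frequency | 2.13, 1.35 | 2 | −0.74 to +0.69, one at 0.05 | 0.80 |
| All symptoms 50/30/15/5 | Ordered 0-3 | 3.87, 0.60 | 1 | 0.69 to 0.70 | 0.89 |
| All symptoms 50/30/15/5 | Frequency | 3.84, 0.60 | 1 | 0.69 | 0.90 |

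With mixed patterns, an eigenvalue-above-1 rule keeps a second factor that does not exist. When every symptom falls steadily with severity, the result hardly changes. Ridit scores perform like ordered scores in the mixed setting (first eigenvalue 3.91, one above 1, correlation 0.91).

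**The case against.** The strongest reply is that the sentence is loosely worded and may not mean sample frequency at all. Occurrence probability could stand for a cumulative score, or for a 0-1 degree to which a sign is present, and both would keep the order. This stands as a possibility. But the text mentions neither, and someone coding the data from it would produce the faulty code. If another score was meant, the sentence still needs correcting.

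The affected variables are also unknown. Many of the signs in section 2.8 may be plain presence/absence items under the second rule. That section lists "Score of TCM syndrome score scale", but section 2.12 does not name the scale among the data entered. The share of inputs affected therefore cannot be stated.

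A reader might infer that the rule always destroys severity order, or that the syndrome elements and the model must be wrong even with perfect data. The documents do not support that. Where frequencies rise or fall steadily with severity, the order is kept or merely reversed. A reversal common to all graded symptoms leaves the eigenvalues almost unchanged, although these symptoms then load with the opposite sign to the binary items. Complete loss of a variable needs exactly equal frequencies. A nonlinear network can in principle undo distinct codes, because they only relabel the grades; it cannot undo ties.

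The dependence on the sample is conditional too: section 2.12 does not say that probabilities are recomputed by stage or in new data.

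**Conclusion.** The point holds in limited form. The stated rule, taken literally, is unsound because it does not in general preserve severity order. It can change the size and sign of loadings, the number of factors retained and the symptom weights.

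The size in this study cannot be determined from the article. The simulated harm (a spurious second eigenvalue of 1.35, and a correlation with the true factor of 0.80 instead of 0.92) rests on assumed mixed patterns, four grades and a single factor with loading 0.7. If all graded symptoms share a steadily falling pattern, the harm is close to nil apart from sign. For the network, the risk is mainly ties and codes recomputed in other data.

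The rule should be corrected before the data are coded, since it governs the inputs to the main analysis.

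**What to change.** Replace the sentence on graded data in section 2.12 with a rule such as: each graded variable takes ordered scores set in advance (for example 0/1/2/3 rescaled to 0-1), with absence at 0 and the same direction as the binary items, and with identical codes in every stage and in the verification data. List the variables to which it applies.

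If a cumulative-probability (ridit) score was intended, say so, compute it once in the training data and freeze it. Ridits also depend on the sample and give absence a nonzero value (0.50/2 = 0.25 when half the patients have none), so they do not align with the 0/1 items as fixed scores do.

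The cost is one sentence and a recode. The records are retrospective, so no data are lost. The small downside is that equal-interval scores assume equal spacing between grades; a sensitivity factor analysis on polychoric correlations would check this.

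### Separate principal component analyses by stage, with factors kept by scree plot and eigenvalue, cannot by themselves tell true stage differences from sampling noise

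*Protocol article*

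**What the plan says.** The second objective in the Abstract begins: "To find out the relationship between different stages of PSD and TCM syndromes". It goes on to ask which syndromes dominate at each stage and how they evolve.

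Section 2.12 derives the syndrome elements by factor analysis "in different stages (acute stage, consolidation stage, maintenance stage, and withdrawal stage"). It continues: "Principal component analysis is performed for each group. According to the values of gravel map and characteristic root, the significant common factors are extracted". The gravel map is the scree plot and the characteristic root is the eigenvalue; no cut-off is given. Elements are then classified from the symptoms on each factor, and the syndrome types and the neural network follow. Qualitative items enter as binary variables: "The assignment principle of qualitative variables is 1 for existence and 0 for nonexistence". Graded items have their own coding rule.

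Section 2.11 justifies the sample size for the neural network on the whole sample ("it is suggested that sample size should be not less than 200") and concludes that "this study plans to collect 300 cases". It gives no number per stage.

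Section 2.8 lists the TCM syndrome, the syndrome score and the stage among the main indicators. The Introduction argues for working by stage, because mixing stages could mislead.

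**The concern.** Each stage gets its own factors, chosen and labelled from its own data. Two stages with the same underlying symptom structure will still give different sample correlations. They may therefore keep different numbers of factors and group symptoms differently. If the per-stage lists are then read side by side, sampling variation can pass for a change of syndrome with stage, which is what objective 2 sets out to find. Section 2.12 builds the syndrome types and the diagnostic model after this step, so unstable elements may carry forward.

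The retention rule makes this worse. The eigenvalues of a correlation matrix of p items sum to p, so their mean is exactly 1. If the items are unrelated, sampling spread alone puts nearly half of them above 1.

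**Working it through.** **Inputs from the protocol article.** 300 cases (2.11); a floor of 200 and 20% verification data (2.11); four stages (2.12); one extraction per group, with retention by scree and eigenvalue (2.12); 0/1 coding of qualitative items (2.12).

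**The plan's own figure.** Inflating 200 for a 20% hold-out gives 200 / (1 − 0.20) = 250, or 200 × 1.20 = 240 by the cruder variant. Neither is 300. The text also cites hospital admissions ("Combined with the admission status of PSD in this hospital and 20% verification data"), and 300 × 0.80 = 240 training cases clears the floor of 200. So 300 is a feasibility figure and not an arithmetic error. It says nothing about analysis by stage.

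**Cases per stage.** 300 / 4 = 75 if equal, or 240 / 4 = 60 if the verification cases are held out first. Rare stages would have fewer.

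**Simulation with no true stage difference.** Assumptions not in the document: 30 or 60 binary symptoms, six factors, latent loadings 0.6 or 0.8, prevalences 10–60%, varimax rotation, an eigenvalue cut-off of 1, an automated scree elbow, and stage sizes 75/75/75/75 or 120/90/60/30. There were 100 runs per setting. Each symptom is assigned to the factor on which it loads highest. Agreement between two stages is the adjusted Rand index, (S − E) / (½(A + B) − E). Here S is the number of symptom pairs grouped together in both stages, A and B are the numbers in each stage, and E = A·B / C(p,2). A value of 1 means identical groupings and 0 means chance agreement.

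| Stage sizes | Symptoms | Loading | Mean factors kept (truth 6) | Number differs, eigenvalue | Number differs, scree | Agreement, eigenvalue rule | Agreement, 6 factors fixed |
|---|---|---|---|---|---|---|---|
| 75 each | 30 | 0.6 | 11.7 | 95% | 100% | 0.16 | 0.32 |
| 75 each | 30 | 0.8 | 9.0 | 85% | 94% | 0.73 | 0.98 |
| 75 each | 60 | 0.6 | 21.6 | 94% | 100% | 0.09 | 0.56 |
| 75 each | 60 | 0.8 | 17.1 | 98% | 73% | 0.56 | 0.99 |
| 120/90/60/30 | 30 | 0.6 | 11.5 | 91% | 100% | 0.14 | 0.28 |
| 120/90/60/30 | 30 | 0.8 | 8.8 | 98% | 97% | 0.65 | 0.82 |
| 120/90/60/30 | 60 | 0.6 | 20.9 | 100% | 100% | 0.08 | 0.43 |
| 120/90/60/30 | 60 | 0.8 | 16.6 | 95% | 91% | 0.53 | 0.88 |

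**Pure noise.** With 75 patients and unrelated symptoms, the eigenvalue rule kept about 13 of 30 components (13.24 / 30 = 44%) and about 24 of 60 (24.22 / 60 = 40%).

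**Is it only sample size?** No. With 300 per stage the number kept still differed in 83–92% of runs, although agreement rose to 0.32–0.98. The retention rule is part of the problem.

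**Second set of assumptions.** With 40 binary symptoms, five factors (number fixed correctly), and two groups of 75 from one population, mean factor congruence was 0.47, 0.69 and 0.83 at loadings 0.5, 0.6 and 0.7. The share of symptoms moving to another factor was 54%, 19% and 2%. A repeat run gave 0.48, 0.71 and 0.84, with 51%, 15% and 1.5%. A further run with five true factors and four stages of 75 kept 8 to 23 factors, and the number differed in 86–98% of runs. Parallel analysis on the pooled 300 recovered about 5.

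**What a common solution does.** One extraction on all 300 (six factors), with scores compared across stages by Kruskal–Wallis tests at 0.05 / 6, gave a false difference in 2–10% of runs per setting. The mean over the eight settings is (2 + 6 + 6 + 2 + 4 + 2 + 7 + 10) / 8 = 4.9%. This run used the true number of factors, which favours the common solution.

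**The case against.** The strongest reply is that working by stage is a reasoned choice. The Introduction warns that mixing stages could mislead. A pooled extraction assumes the common structure that is in question, and differences in symptom prevalence between stages can themselves create correlations in pooled data. This stands, and it is why the per-stage solutions should be kept and not replaced.

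Second, instability depends on unknown loadings. With the right number of factors and loadings of 0.8, agreement was 0.82–0.99; at 0.7, only about 2% of symptoms moved. A differing number of factors can also mean one extra weak factor, which is not the same as a different main syndrome. Both points stand. They limit the claim but do not rescue the retention rule.

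Third, the plan combines scree and eigenvalue and states no cut-off, so the eigenvalue-above-1 results test only one part of it. That is fair, but the automated scree elbow also gave differing numbers in 73–100% of runs.

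Fourth, a fuller document may give the rotation, the cut-off and a formal stage comparison. Their absence from an article is not held against the plan. The point concerns the method that the article does state.

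A reader might infer that objective 2 cannot be answered, or that any reported stage difference would be an artefact. The documents support neither. Section 2.8 records syndrome, syndrome score and stage for each patient, so they can be compared directly, and 2.12 also draws on other TCM and Western indexes to settle the syndrome types.

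**Conclusion.** The point holds in a limited form. Separate extraction by stage with scree and eigenvalue retention cannot by itself separate true stage differences from sampling noise. With identical structure in every stage, the eigenvalue rule kept about 9 to 22 factors where six were true, and the number differed between stages in 85–100% of runs. Symptom groupings were unstable at loadings of 0.6, and fairly stable at 0.8 once the number of factors was right.

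The direction was the same in every setting tried. The exact rates rest on assumed symptom counts, loadings, rotation, cut-off, stage sizes and all-binary items; the document gives the share of binary items nowhere. Reading each group as each stage follows from the preceding sentence but is not stated outright. This is a cheap improvement to the analysis and does not undermine the study as a whole.

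**What to change.** Amend 2.12 in four ways.

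1. Set the number of factors by parallel analysis instead of scree and eigenvalue, using tetrachoric or polychoric correlations where items are binary or graded.
2. Add one common solution on all 300 cases. Compare its factor scores, and the recorded syndromes and syndrome scores of 2.8, across the four stages, with effect sizes and intervals.
3. Keep the per-stage solutions, but claim that structure differs by stage only if the difference exceeds what resampling gives by chance, for example by permuting stage labels. Permutation also responds to differences in symptom prevalence, so report prevalence by stage beside it.
4. Do not adjust the main comparison for time since stroke. It overlaps with stage and could remove part of the effect under study.

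No new patients or data items are needed. The cost is modest analysis work outside SPSS 17. The common solution assumes a shared factor structure, which step 3 examines. Tetrachoric correlations can be unstable for rare symptoms in small stages, and the simulations above used ordinary correlations, so the gain from that change was not measured.
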